## Abstract

**Introduction:**

Recurrent pregnancy loss (RPL) is defined as the occurrence of two or more spontaneous pregnancy losses from the time of conception until 24 weeks of gestation. Currently, an underlying cause can be identified in only a minority of the losses. Potentially, an impaired maternal immune response targeting the semiallograft pregnancy may lead to miscarriage. While prior studies have explored the use of immune-suppressing corticosteroids to modulate the maternal immune system and hopefully improve pregnancy outcome, the absence of sufficiently powered randomised controlled trials (RCT) underscores the need for further research. The primary aim of this study is to evaluate if prednisolone administration in early pregnancy (20 mg daily for 6 weeks, then tapering doses for 2 weeks) in women with unexplained RPL leads to a higher live birth rate (LBR) in comparison to placebo. Additionally, the study assesses the tolerability, safety and the cost-effectiveness of this intervention. Finally, we will explore the effect of prednisolone in various subgroups (based on maternal age, number of previous pregnancy losses, presence of specific antibodies and pre-pregnancy endometrial immune cell level).

**Methods and analysis:**

This ongoing multicentre, double-blind RCT will randomise 490 women with unexplained RPL and pregnancy <7 weeks to receive either prednisolone or placebo. Each participant will be followed up for 1 year, with digital questionnaires to assess depression, anxiety, medical expenses and productivity loss. We will also collect data on maternal and paternal demographics and neonatal outcomes. The sample size of 490 participants was calculated according to a minimally important increase in LBR of 12% (expecting a LBR of 63% in the general RPL population), including loss to follow-up (estimated at 5%). The analysis will follow the intention-to-treat principle.

**Ethics and dissemination:**

This study was submitted under the Clinical Trial Regulation (CTR) in Clinical Trials Information System (CTIS) for assessment by the Central Committee on Research Involving Human Subjects (CCMO) under Clinical Trial number: 2023-503220-76-01. It received full approval on 29/01/2024. Study findings will be presented at conferences and published in a peer-reviewed journal. Participants will be informed about the results by publishing them on the publicly available website of the study.

**Trial registration number:**

This trial is registered in ClinicalTrials.gov (ID NCT05725512) and in CTIS (2023-503220-76-01).

STRENGTHS AND LIMITATIONS OF THIS STUDYThis is the first adequately powered randomised controlled trial to investigate the effect of prednisolone on live birth rate in women with unexplained RPL.In addition, we study the tolerability, safety and the cost-effectiveness of this intervention, to promote implementation of study results in daily practice.The study allows to explore the effect of prednisolone amongst various decidual immune cell populations.A limitation of the study might be that the study is underpowered to detect differences in effects between subgroups. Further research must then be conducted with targeted designs and adequate sample sizes to specifically investigate and validate the observed effect within relevant subgroups.

## Introduction

 The most common complication in pregnancy is miscarriage, defined as the spontaneous loss of the foetus before 24 weeks of gestation.^1^ The overall chance for pregnancy loss is between 10% and 15% if maternal age is <35 years.^2^ Recurrent miscarriage, also known as recurrent pregnancy loss (RPL), is defined as two or more (non-)consecutive losses before 24 weeks of gestation. RPL affects approximately 3% of couples trying to conceive.^3^

Underlying factors contributing to RPL include a variety of conditions: maternal antiphospholipid syndrome, congenital uterine abnormalities, parental balanced translocations, thyroid antibodies and endocrine abnormalities (eg, diabetes).^4^,^13^ Additionally, numerous risk factors are associated with RPL, including advanced maternal age,^14^ abnormal body mass index (BMI; either high or low),^15 16^ smoking and other intoxications^17 18^ and specific medication usage.^18^,^20^ These risk factors contribute to abnormal fetal chromosomal development (eg, triploidy and autosomal trisomy^21^). Indeed, 50% of sporadic pregnancy losses are caused by fetal aneuploidy. In women with a higher number of pregnancy losses, however, the likelihood of a euploid pregnancy loss rises with each subsequent pregnancy loss.^22^ Presently, routine genetic analysis of miscarriage tissue is not recommended, leaving approximately 50% of recurrent miscarriages without an underlying factor. Limited understanding of the mechanisms underlying RPL leads to a lack of effective interventions. Numerous studies have thoroughly explored treatments for couples facing unexplained RPL, including human chorionic gonadotropin therapy,^23^ acetylsalicylic acid,^24^ heparin,^24 25^ progesterone^26^ (which is now only indicated in the case of vaginal blood loss in pregnancy after three or more pregnancy losses^27^) and vitamin supplementation.^28^ Immune-related interventions, namely paternal leucocyte immunisation^29^ and intravenous immunoglobulin,^30^ also showed no improvement in the LBR. Consequently, current clinical management is primarily focused on providing supportive care.^3^

As the foetus is a semiallograft, which is accepted by the maternal immune system in healthy pregnancy, many studies proposed the involvement of immunological mechanisms in RPL. These include the level and function of uterine natural killer (uNK) cells, macrophages and regulatory T cells.^31^,^34^ Glucocorticoids, such as prednisolone, could potentially improve the intrauterine environment and implantation by positively influencing these cells to adopt a more tolerogenic phenotype towards the embryo. Glucocorticoids therefore represent a potentially useful therapy in patients with RPL with suspected underlying immunological cause. So far, three randomised controlled trials (RCT) studied the effect of prednisolone on pregnancy outcome in patients with RPL, showing hopeful results.^35^,^37^ However, these trials were inadequately powered to investigate effectiveness, their inclusion criteria differed and in two trials, heparin and acetylsalicylic acid were used as co-intervention. In addition, most patients were selected based on the NK cell density in prior uterine biopsy, though this has not yet proven to be a valid biomarker.^38^ Considering the potential risks and consequences associated with administering glucocorticoids,^39^ a clinical trial within the general population suffering from unexplained RPL with adequate randomisation and power is urgently needed.

### Objective

To examine whether administering prednisolone before 7 weeks of gestation to women with unexplained RPL results in higher live birth rate (LBR) compared with the administration of placebo treatment.

## Methods and analysis

### Design and setting

The PREMI-study is an ongoing—the study started on 29-01-2024 (actual), primary completion 29-07-2026 (estimated) –multicentre, double-blind, placebo-controlled RCT that is being conducted in 12 academic and non-academic centres within the Netherlands.

### Participants and eligibility criteria

Eligible patients are women aged 18–39 years with ‘unexplained recurrent pregnancy loss’, defined as the loss of two or more pregnancies, without a known cause for RPL (such as antiphospholipid syndrome, congenital uterine abnormalities or abnormal parental karyotype). As fetal aneuploidy is the most common cause of pregnancy loss, but more often not tested in case of pregnancy loss, women with potentially aneuploid losses are eligible to participate. The diagnosis of unexplained is based on the latest ESHRE guideline (including biochemical pregnancy losses).^3^ Patients who meet any of the following criteria will be excluded from participation in this study:

Instable, or exacerbation of, auto-immune diseases such as thyroid disease or inflammatory bowel disease.Diabetes mellitus requiring medical treatment.Current treatment with systemic corticosteroids (for any indication) or other immunosuppressive medication.Simultaneous enrollment in any other trial that studies the effectiveness of an intervention in RPL or previous enrolment in the PREMI trial.Contraindications to prednisolone use.Use of drugs with known interaction with prednisolone.

Patients can enroll in the study either during early pregnancy (<7 weeks gestation), with randomization performed at enrollment, or before conception if they ave an active desire to conceive, with randomization delayed until pregnancy is confirmed. Both women who conceive spontaneously and those who conceive through artificial reproductive techniques are eligible for participation.

### Procedures, recruitment and randomisation

The total (planned) enrolment period of the study is 30 months, with a subsequent 12 month follow-up. Eligible patients will be identified by local research coordinators and/or staff members trained in ‘good clinical practice’ at participating hospitals. Patients will receive verbal, written and/or video-animated information. When signing the informed consent form, non-pregnant patients will be requested to collect and send in menstrual blood from the first 24 hours of menstruation to the coordinating centre (Leiden University Medical Centre, LUMC) for the isolation of endometrial immune cells. Upon confirmation of pregnancy (urine or blood test) <7 weeks gestational age, randomisation takes place, in a 1:1 ratio, using Castor EDC with variable randomisation blocks (4, 6 and 8). Patients will be assigned to the intervention or placebo group, with allocation blinded to investigators, participants, clinicians and research coordinators.

Data will be collected in a web-based registration system, Castor (CDMS 2023.4). Once a patient is randomised, the research nurse will collect data in the electronic case report form provided in Castor. Database cleaning will be conducted by internal consistency checks and identification of database entries outside expected ranges. Patients will receive standard care with their own treating physician or midwife. All collected data will be coded, processed and stored with adequate precautions to ensure patient confidentiality. This is described in a separate data management plan.

### Intervention and placebo

The intervention entails an 8-week prednisolone or placebo treatment regimen, administered orally in the form of tablets (manufactured by the clinical pharmacist of the Leiden University Medical centre), starting before 7 weeks of gestational age. This treatment includes a daily dosage of 20 mg for 6 weeks, followed by 1 week at 10 mg daily, and concluding with 1 week at 5 mg daily. The placebo and prednisolone treatments are identical in appearance: white circular flat-faced tablets, with a break line, an average weight of 160 mg and a diameter of 8 mm. The prednisolone tablets and placebo tablets are identical in pharmaceutical form and qualitative composition (except for the active substance prednisolone). The tablets contain either 20 mg of prednisolone for the first 6 weeks or 5 mg tablets for the tapering phase. Upon receiving their medication, participants will be given comprehensive instructions to ensure proper usage and adherence to the treatment regimen. Patients are considered compliant when at least 80% of the prescribed treatment regimen is followed (monitored in the medication diary).

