### Outcome measures

The following outcomes and variables will be collected during this trial;

Primary outcome: live birth, defined as the birth of a living child beyond 24 weeks of gestational age.Pregnancy course monitoring: ultrasound biometric outcomes, gestational age at time of pregnancy loss (if applicable).Pregnancy complications, such as hypertensive disorders and gestational diabetes.Delivery and postpartum details, including delivery method and postpartum complications.Neonatal information: weight, percentile, presence of congenital abnormalities, gestational age and other relevant factors.

Additionally, digital questionnaires will be administered to patients at various intervals during the follow-up period. These include:

Hospital Anxiety Depression scale and EQ-5D-5L at randomization, 3, 6, and 12 months post-randomization to assess maternal quality of life.iMedical Consumption Questionnaire at 6 and 12 months post-randomization to evaluate maternal medical expenses.iProductivity Cost Questionnaire (iPCQ) at 6 and 12 months to measure maternal productivity loss.Medication diary: common side effects of prednisolone (nausea and vomiting, mood swings, hypertension, hyperglycaemia and weight gain) will be monitored using digital medication diaries to evaluate compliance and adverse reactions.

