### Statistical analysis

#### Data analysis

We engaged the expertise of statisticians and methodologists to ensure meticulous planning of the data analysis. Additionally, a health technology assessment (HTA) expert was employed to contribute to the cost-effectiveness analysis (CEA) of the research.

The analysis of the gathered data will involve several methodological approaches:

Demographic information about the studied population will be presented using descriptive statistics, depicted in tables.

The primary outcome is live birth. We will first report the observed number (and percentage) of live births in the treatment and placebo groups. Following the recommendations of the The United States Food and Drug Administration (FDA) for covariate adjustment in clinical trials,^47^ to increase power, we compared the LBRs between the intervention and control group using a multivariable logistic regression analysis, taking into account strong predictors of pregnancy loss, in this case, maternal age and previous number of pregnancy losses.^3^ From this multivariable model, we will derive an estimate of the marginal treatment effect, expressed as an absolute risk difference, along with 95% CI, using standardisation and bootstrapping. The statistical significance threshold will be set at p<0.05, and all analyses will be performed using SPSS or R.

Secondary outcomes and subgroup analysis

Next to the primary outcome, we will consider the following secondary outcomes

Pregnancy loss, defined as the spontaneous demise before the 24th week of gestation.Ongoing pregnancy, defined as viability of the fetus beyond the 12th week of gestation.Tolerability (defined as percentage of non-compliance due to side-effects).Safety of prednisolone (including congenital abnormalities, gestational weight, SAEs and SUSARs).Side-effects to the mother or the fetus and the cost-effectiveness of the treatment.

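### Tolerability is tied to the 80% compliance rule, so a stop for side-effects late in the course is not counted, and the denominator is left open

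*Protocol article*

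**What the plan says.** The Protocol article, under Intervention and placebo, describes the course: "The intervention entails an 8-week prednisolone or placebo treatment regimen", made up of "a daily dosage of 20 mg for 6 weeks, followed by 1 week at 10 mg daily, and concluding with 1 week at 5 mg" per day. On tablet strength it says: "The tablets contain either 20 mg of prednisolone for the first 6 weeks or 5 mg tablets for the tapering phase". The same section gives the compliance rule: "Patients are considered compliant when at least 80% of the prescribed treatment regimen is followed (monitored in the medication diary". It names no counting unit.

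The list of secondary outcomes, under Statistical analysis, builds on that rule: "Tolerability (defined as percentage of non-compliance due to side-effects". It states no denominator. A separate entry in the same list reads "Side-effects to the mother or the fetus and the cost-effectiveness of the treatment".

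Under Outcome measures, side-effects "will be monitored using digital medication diaries to evaluate compliance and adverse reactions", and the pregnancy data include "gestational age at time of pregnancy loss (if applicable".

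The Abstract names tolerability among the things the study assesses. The secondary outcomes are to be compared between arms at the 5% significance level.

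**The concern.** Tolerability should tell a reader how often women gave up the drug because of what it did to them. Here it is routed through a compliance threshold that serves another purpose, namely to say whether enough of the course was taken. A woman can pass the threshold and still abandon treatment because of side-effects. The definition then records her as compliant, and so as having tolerated the drug.

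The denominator is a second, weaker point. The wording can be read as the proportion of women who were non-compliant because of side-effects, or literally as the proportion of non-compliance that side-effects explain. These two readings behave very differently in a trial where many pregnancies may end during treatment and the arms are expected to differ in how many do.

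What is at stake is one named secondary outcome and its comparison between arms, not the primary result.

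**Working it through.** **Figures the plan states.** The compliance rule has no derived figure to reproduce. The design rates used in step 2 are those behind the sample size, which does reproduce: 63% against 75%, two-sided 5%, power 80%, no continuity correction, gives 232 per arm, or 464. Then 464 / 0.95 = 488.4, so 489, made even as 490.

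**Step 1. When the 80% mark is passed, with no missed doses.** Inputs are from Intervention and placebo. The tablet count takes 10 mg as two 5 mg tablets.

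| Unit | Full course | 80% of it | First day at or above 80% | Days left of 56 |
|---|---|---|---|---|
| mg | 42×20 + 7×10 + 7×5 = 945 | 756 | day 38 (38×20 = 760) | 18 (32%) |
| days | 56 | 44.8 | day 45 | 11 (20%) |
| tablets | 42×1 + 7×2 + 7×1 = 63 | 50.4 | day 47 (42 + 5×2 = 52) | 9 (16%) |

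A permanent stop for side-effects in those last days leaves the woman at or above 80%, so it is not an event. A woman who missed doses earlier passes the mark later, so these windows are the longest possible. The percentages are shares of the course. They would be shares of stops only if stops were spread evenly over it, which the article gives no ground to assume. Without a stop rate, the number missed cannot be computed.

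**Step 2. What the denominator does.** From Sample size calculations, 37% of control and 25% of prednisolone women are expected not to have a live birth. The rest is assumption:
- drug stops at pregnancy loss;
- a share f of the pregnancies without live birth, 50% to 90%, end before the 80% mark;
- these losses are evenly spread, so such a woman has on average half the exposure;
- the risk s of a counted side-effect stop is the same in both arms, 5% or 10%;
- there is no other cause of non-compliance.

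With l = 0.37f (control) or 0.25f (prednisolone):
- side-effect non-compliers per woman randomised: T = s × (1 − l/2);
- all non-compliers: T + l × (1 − s/2);
- share of non-compliance: T / [T + l × (1 − s/2)].

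Worked case, f = 0.5 and s = 0.05. Control: l = 0.185, T = 0.05 × 0.9075 = 0.0454, all non-compliers 0.0454 + 0.185 × 0.975 = 0.2258, share 20.1%. Prednisolone: l = 0.125, T = 0.05 × 0.9375 = 0.0469, all non-compliers 0.0469 + 0.125 × 0.975 = 0.1688, share 27.8%.

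| f | s | Per woman randomised, control vs prednisolone | Share of non-compliance, control vs prednisolone |
|---|---|---|---|
| 50% | 5% | 4.54% vs 4.69% | 20.1% vs 27.8% |
| 90% | 5% | 4.17% vs 4.44% | 11.4% vs 16.8% |
| 50% | 10% | 9.07% vs 9.38% | 34.1% vs 44.1% |
| 90% | 10% | 8.34% vs 8.88% | 20.9% vs 29.3% |

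Side-effect stopping is equal by construction. Per woman randomised, the arms differ by about 0.1 to 0.5 points. As a share of non-compliance they differ by about 5 to 10 points, and prednisolone looks worse tolerated only because fewer pregnancies were lost.

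**The case against.** The strongest defence has four parts.

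*The missed window is small and late.* By days or tablets it lies wholly inside the taper (days 43 to 56); only the mg count reaches earlier. Under Monitoring and safety, the article reports an earlier feasibility trial in which no side-effect was severe enough to make women stop. This stands as a reason to expect few missed events. It does not make the classification right, and a trial that sets out to measure tolerability should not rest on that expectation.

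*Side-effects are reported anyway.* They are a separate secondary outcome and are recorded in the diary, so the symptoms are not lost from the safety data. But a list of symptoms does not count who stopped because of them.

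*Unit, denominator and handling of losses belong in the analysis plan.* For the unit alone this is fair: it is detail that can be settled there. The planned logistic regression also points to an outcome per woman, the harmless reading of the denominator. The link between tolerability and the 80% rule is different, because the article itself fixes it.

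*Pregnancy loss does not bias tolerability.* A reader might infer more: that loss itself makes women non-compliant, more often on placebo, and so creates a false difference in tolerability. With f from 50% to 90%, loss-related stops would be 18.5% to 33.3% on control and 12.5% to 22.5% on prednisolone, a gap of 6 to 11 points. That gap is in all-cause non-compliance, which is not a listed outcome. The restriction to side-effects keeps these stops out of the numerator. The article commits to intention-to-treat and describes no compliant-only analysis. It gives no timing of losses, and does not say that drug stops at a loss or that later doses still count as prescribed. The objection holds against this stronger reading.

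**Conclusion.** The point holds in a limited form. The two definitions together misclassify a permanent stop for side-effects after the 80% mark. This follows from the text and the dosing schedule alone and covers at most the last 9 to 18 of 56 days, depending on the unit. The number of women affected is unknown.

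The denominator point is conditional. It matters only if tolerability is reported as a share of all non-compliance and drug stops at pregnancy loss. Per woman randomised, the distortion of about 0.1 to 0.5 points is far below sampling error: with 245 per arm, the standard error of a difference at rates of 5% and 10% is √(2 × 0.05 × 0.95 / 245) = 2.0 points and √(2 × 0.10 × 0.90 / 245) = 2.7 points.

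The documents do not support saying that pregnancy loss invalidates the tolerability outcome. The change is still worth making, because it corrects a named secondary outcome at almost no cost.

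**What to change.** Define tolerability as permanent discontinuation of study drug because of side-effects, at any time from first dose to the earlier of planned end of treatment or end of pregnancy. Report it by arm, per woman who started treatment, with pregnancy loss treated as a competing event. Report adherence separately, as doses taken over doses due up to that same date, with the unit stated, and keep the 80% cut as a descriptive summary only. This fixes what is counted and takes no position on how treatment is managed after a loss.

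The cost is a small change of definition in the protocol and the analysis plan, which the article says will be published before the database closes. The medication diary and the gestational age at loss are already collected. The tolerability percentage may look slightly less favourable.

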### Baseline information

The baseline information is collected at randomisation in Castor EDC and it encompasses:

Maternal medical history and demographics: number of previous pregnancy losses, age, parity, BMI and relevant medical conditions.Paternal information and demographics: biometric data, history of subfertility or infertility, and relevant intoxications.

